## Abstract

Background: Chronic spinal cord injury (SCI) significantly accelerates morbidity and mortality, partly due to the increased risk of cardiometabolic diseases (CMD), including neurogenic obesity, dyslipidemia, and impaired glucose metabolism. While exercise and dietary interventions have shown some transient benefits in reducing CMD risk, they often fail to improve clinically relevant disease markers and cardiovascular events. Moreover, SCI also places caregiving demands on their caregivers, who themselves experience health and functional decline. This underscores the need for more substantial interventions that incorporate appropriate physical activity, heart-healthy nutrition, and behavioral support tailored to the SCI population. Objectives: This randomized clinical trial (RCT) protocol will (1) assess the health and functional effects, user acceptance, and satisfaction of a 6-month comprehensive therapeutic lifestyle intervention (TLI) adapted from the National Diabetes Prevention Program (DPP) for individuals with chronic SCI and (2) examine the impact of a complementary caregiver program on the health and function of SCI caregivers and evaluate user acceptance and satisfaction. Caregivers (linked with their partners) will be randomized to ‘behavioral support’ or ‘control condition’. Methods: Dyadic couples comprise individuals with SCI (18–65 years, >1-year post-injury, ASIA Impairment Scale A-C, injury levels C5-L1) and non-disabled SCI caregivers (18–65 years). Both groups undergo lock-step circuit resistance training, a calorie-restricted Mediterranean-style diet, and 16 educational sessions focused on diet/exercise goals, self-monitoring, psychological and social challenges, cognitive behavioral therapy, and motivational interviewing. The outcome measures encompass the cardiometabolic risks, cardiorespiratory fitness, inflammatory stress, multidimensional function, pain, life quality, independence, self-efficacy, program acceptance, and life satisfaction for SCI participants. The caregiver outcomes include multidimensional function, pain, quality of life, independence, and perceived caregiver burden. Discussion/Conclusions: This study evaluates the effects and durability of a structured, multi-modal intervention on health and function. The results and intervention material will be disseminated to professionals and consumers for broader implementation. Trial Registration: ClinicalTrials.gov, ID: NCT02853149 Registered 2 August 2016.

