## 4. Materials and Methods

### 4.1. Trial Design

This is a prospective randomized, controlled, multi-center intervention adopting a within-subjects repeated measures design, examining persons with disability from SCI and their caregivers who will be co-enrolled as dyadic partners. Following eligibility screening, consent, and randomization (of caregivers only), participants will attend two preliminary sessions including wash-in and baseline assessments (serving as ‘own-control’) prior to beginning in one of the two intervention conditions. Two post-intervention assessments will be conducted, one immediately post-TLI (6 months) and one follow-up (12 months). The trial design is summarized below (Figure 1), was approved by the Human Subjects Research Office, Miller School of Medicine, University of Miami (Institutional Review Board No. 20151065, dated 20 July 2016), and is registered as a controlled trial (ClinicalTrials.gov, ID: NCT02853149 on 2 August 2016).

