### 4.4. Randomization

Given the elevated risk of CMD, the reported benefit of intervention studies on mitigating CMD risk [36], including a preliminary report on the TLI [26], and the ethical imperative to provide effective interventions [37], all participants with SCI will undergo a TLI program modeled after the CDC-supported widely adopted National DPP. The intervention program will incorporate population-targeted exercise, nutrition, and behavioral support in the form of a detailed curriculum, all aspects of which have been tested in a federal grant program at the lead center. Following the completion of baseline assessments, caregivers will be randomized to one of two groups using a stratified approach to achieve equal numbers in persons caring for enrolled partners with paraplegia and tetraplegia. Randomization will be performed independently within each stratum by an independent senior researcher using a list generated by the ‘RAND’ function in Microsoft Excel (Microsoft, Miami, FL, USA). Blinding is not achievable in this intervention study, and therefore neither participants nor research staff will be blinded. Participants are randomly sorted based on generated random numbers—a binary response variable, 0 for the control curriculum group and 1 for the CCC group— and their allocation to groups depends solely on their position in the sorted order. This randomization procedure ensures that participants are allocated to the CCC and control groups in an unbiased and unpredictable manner. Randomization of caregivers serves scientific and ethical purposes by allowing for rigorous assessment and ensuring equitable access to the intervention. Caregivers (linked with their partners) randomized to the test condition will undergo a CCC containing information that is similar to that presented to, but independently taught from, their partners. Caregivers randomized to the control condition will learn a time-matched (i.e., attention/time-controlled) curriculum containing generic information on the overall benefits of exercise and nutrition but lacking any specific exercise/nutritional guidelines, self-management strategies, or nutritional/meal composition. This information will be tailored to people without disabilities and include information the caregiver might otherwise find on the internet. All caregivers, irrespective of randomization, will receive SCI-specific material so that they can provide the appropriate support and best care possible in the framework of the TLI.

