## 6. Intervention

### 6.1. SCI Participants

6-Month Supervised Exercise Intervention: Circuit Resistance Training (CRT): The benefits of the CRT—a training algorithm adopted to increase muscular strength and cardiopulmonary endurance—have been described for persons with paraplegia [66,67] and tetraplegia [68]. Study participants will undergo CRT three times weekly on non-consecutive days or two consecutive days and one non-consecutive day for 24 weeks. An exercise technician will assist with the station setup during training. Each session will last approximately 40–45 min and employ resistance training (weightlifting) and endurance activities (reciprocal arm exercise, VitaGlide^®^ (VitaGlide, LLC., Rockledge, FL, USA), RehabMed International, or arm crank ergometry, Colorado Cycle) with interposed periods of incomplete recovery (i.e., heart rate not falling to baseline). The training session will follow a structured sequence. Prior to each session, a 2 min warm-up will be conducted on a Vita-Glide^®^ or arm crank ergometer. The resistance exercises will be performed in pairs, with each pair consisting of two maneuvers performed consecutively. Each maneuver will involve 10 repetitions, with a 6 s movement duration, divided into 3 s for concentric (lifting) and 3 s for eccentric (lowering) phases. Following the resistance exercises, there will be a 2 min period of endurance exercise without applied resistance. This pattern of alternating between resistance and endurance exercises will continue until the subjects complete three rotations through each resistance station. During the first two weeks of each month, the resistive loads for training will be set at 50% of the calculated 1-repetition maximum (1-RM) values obtained from the initial isoinertial strength testing, as previously reported [69]. Subsequently, the loads will be increased to 55% and 60% of the 1-RM during weeks three and four of each month, respectively. To account for the effects of training, the 1-RM for each maneuver will be recalculated during the final training session of every 4-week cycle. Please refer to Table 2 for a summary of the resistance maneuvers.

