### 6.2. CCC Participants

6-Month Supervised Exercise Intervention: The following exercise training protocols are within the accepted guidelines established by the American College of Sports Medicine [62]. The caregiver intervention group will have a 6-month supervised exercise program at the Medical Wellness Center three times weekly that will last 40–45 min. The activities will include resistance training (weightlifting) and endurance training (treadmill and bicycles). The study personnel at the center will oversee the training and testing of the caregivers and establish the exercise prescription. The participants will work with a coach who will direct the exercise performed and work intensity. At the end of each month, the investigators will retest the strength and adjust the weight lifted to match the change in strength due to the training effects. The resistance training protocol consists of seven exercises (chest press, seated row, shoulder press, pulldown, bicep curl, seated dip, and leg press), performed on selectorized resistance training equipment. During the first six weeks, the subjects will be asked to complete one set of 12–15 repetitions of each exercise. When 15 repetitions can be completed comfortably, without fatigue, and in good form, the resistance will be increased by 5–10%. This progression will continue each time the upper end of the repetition range is successfully completed. After six weeks, the repetition range will be adjusted to 8–12 repetitions per set and finally increased to two sets of 8–12 repetitions for weeks 13–72. The cardiovascular exercise prescription will range from 50 to 70% of the estimated VO_2_max for 20–40 min. VO_2_max will be estimated from the data collected during the submaximal treadmill protocol completed during the baseline fitness assessment (i.e., Bruce protocol). Initially, the subjects will start at 50% of the estimated VO_2_max for 20 min and systematically progress to 70% of the estimated VO_2_max for 40 min over the course of the three months. They will then maintain the latter intensity and duration for the remainder of their exercise training program.The 6-Month Nutritional Intervention will be carried out as described above for the SCI participants.The 6-Month Behavioral Intervention will be carried out as described above for the SCI participants.The 6-Month Self-care Extension-Phase Maintenance Program will be as described above for the SCI participants.

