The Caregiver control group will follow a similar schedule but a different curriculum. Although they will have access to the same facilities (Medical Wellness Center) as the intervention group, the control caregiver participants will receive generic (“unstructured’) information about healthy eating and exercising without specific education on food types, exercise guidelines, caloric expenditure, or nutritional composition. The content sources will include online websites, such as *Web*MD Living Healthy (www.webmd.com/living-healthy, (accessed on 2 August 2016)), which typically provide generic information describing the need to exercise (but not providing an exercise prescription), eat well (but not providing a defined diet), and broad lifestyle recommendations. The study personnel at the Medical Wellness Center will oversee the testing of the caregivers without disability but will not establish any specific exercise prescription or training at any time of the intervention. The caregivers will be instructed by the Medical Wellness Center regarding the use of the facilities and safety guidelines.

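### The caregiver control is labelled attention/time-controlled, but only the taught sessions can be matched; the randomised contrast estimates the whole CCC package against generic information

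*Protocol article*

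**What the plan says.** Only caregivers are randomised (Section 4.1: "randomization (of caregivers only"), so CCC versus control is the trial's one randomised comparison. It carries Objective II (caregiver outcomes) and Objective III (added benefit to the SCI partner).

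The article describes the two arms in several ways:

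- **Abstract:** "Caregivers (linked with their partners) will be randomized to ‘behavioral support’ or ‘control condition". A later sentence gives the exercise, diet and educational sessions to both groups. If that means SCI participants and all caregivers, it does not fit the control caregivers of Section 6.2.
- **Section 4.4:** the CCC is presented as information similar to that given to the SCI partner but taught separately. Of the control it says: "Caregivers randomized to the control condition will learn a time-matched (i.e., attention/time-controlled) curriculum containing generic information".
- **Section 6.2, CCC arm:** "The caregiver intervention group will have a 6-month supervised exercise program at the Medical Wellness Center three times weekly that will last 40–45 min". On staff contact: "The participants will work with a coach who will direct the exercise performed and work intensity". Strength is retested monthly, and the diet, behavioural and maintenance components follow the SCI programme.
- **Section 6.2, control arm:** "The Caregiver control group will follow a similar schedule but a different curriculum". Controls receive generic website-type material, access to the same facility, and instruction on its use and safety. Staff oversee their testing, "but will not establish any specific exercise prescription or training at any time of the intervention".

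**The concern.** An attention control is meant to hold staff time and contact equal, so that a difference between arms can be credited to what was taught. Section 4.4 claims that property, but the arms described in Section 6.2 do not have it. They differ at once in taught content, supervised exercise, prescribed diet and coach contact.

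Section 4.4 also says that neither participants nor research staff are blinded. Self-reported pain, function, social satisfaction, anxiety and treatment credibility can respond to attention alone. Under the present label, a CCC–control difference in caregivers, or a benefit passing to the SCI partner, could be reported as an effect of content or behavioural support with attention already accounted for. No later analysis can restore that control, because attention and content are fully confounded by arm.

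**Working it through.** The article gives no contact hours for either arm, so there is no stated figure to reproduce. The hours below are built from its components.

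**Inputs**
- CCC exercise: 3 sessions a week of 40–45 min for 6 months (Section 6.2).
- Weeks: 24, stated for the SCI exercise programme in Section 6.1 ("Study participants will undergo CRT three times weekly on non-consecutive days or two consecutive days and one non-consecutive day for 24 weeks"). The CCC exercise text says only 6 months, so 26 weeks is shown as an alternative. The same text also gives a resistance schedule for weeks 13–72, which does not fit a 6-month programme and needs reconciling; it is not used here.
- Taught sessions: 16 of 30–60 min (Section 6.1, applied to the CCC by Section 6.2).
- Control: the same taught hours. This is an assumption, taken from the time-matched wording.
- Scheduled assessments are the same for both caregiver arms in Table 1 and are left out.

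**Coached exercise, CCC arm** (sessions = 3 × weeks; hours = sessions × minutes / 60)

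| Weeks | Sessions | Hours at 40 min | Hours at 45 min |
|---|---|---|---|
| 24 | 3 × 24 = 72 | 72 × 40/60 = 48 | 72 × 45/60 = 54 |
| 26 | 3 × 26 = 78 | 78 × 40/60 = 52 | 78 × 45/60 = 58.5 |

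**Taught sessions:** 16 × 30/60 = 8 h to 16 × 60/60 = 16 h.

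**Total staff contact at 24 weeks if only the taught sessions are matched**
- CCC: 48 + 8 = 56 h to 54 + 16 = 70 h. Control: 8 to 16 h.
- Ratio = (exercise + taught) / taught, with the same taught hours in both arms. Lowest: (48 + 16)/16 = 4.0. Highest: (54 + 8)/8 = 7.75.
- At 26 weeks: (52 + 16)/16 = 4.25 to (58.5 + 8)/8 = 8.3.

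**What would close the gap.** At 24 weeks, controls would need a further 48–54 h of staff contact. That is 48 extra one-hour sessions at the least (48/1) and 108 half-hour sessions at the most (54/0.5). Nothing of the kind is described.

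**Both readings of the label.** Section 4.4 uses the word curriculum in a broad sense when it describes the SCI programme: exercise, nutrition and behavioural support together. If the time-match is read that broadly, it covers exercise and conflicts with the exclusion of training in Section 6.2. If it is read narrowly, it covers the taught sessions only and leaves the coached exercise unmatched. Attention is not held constant on either reading.

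**Exposed outcomes.** Table 1 has 12 caregiver rows. Six are measured: body mass, endurance, strength, HOMA2, TC:HDL and inflammatory markers. Six are self-reported: diet log, function, pain, social satisfaction, anxiety/depression and treatment credibility.

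**The case against.** The strongest reply is that Section 6.2 lists exercise, diet, behavioural and maintenance components under the CCC, and Objective II refers to the CCC as a programme. On that reading the extra exercise and coaching are the intervention itself, and the comparison is a sound randomised test of a package. This stands. A reader might infer that the contrast is uninterpretable or that it says nothing about the CCC. The article does not support that: what is lost is only the separation of content from attention.

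Second, time-matched qualifies the curriculum that controls learn, and controls follow a similar schedule at the same facility. This stands in part. Total control hours are nowhere stated, so the 4- to 8-fold ratio is conditional, and it would be wrong to present 8–16 h as the documented control total. Time at the facility might even be similar. But unsupervised access is not coached attention, and the gap in supervised contact follows directly from the text.

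Third, a reader might infer that most caregiver outcomes are exposed to attention effects. Table 1 shows six of 12 self-reported, and one of those, treatment credibility, measures acceptance rather than health.

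Fourth, Section 6.2 already sets out both arms, so a careful reader can see what is delivered. That is true, but the label in Section 4.4 and the description in the Abstract still claim something different.

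**Conclusion.** The attention/time-controlled label is wrong as written. At most the taught sessions, 8–16 h, can be matched. CCC caregivers receive about 48–54 h of coached exercise (52–58.5 h over 26 weeks) and a prescribed diet, none of which controls get. If only the taught sessions are matched, staff contact at 24 weeks is about 4 to 8 times higher in CCC. That ratio rests on two assumptions: 24 weeks carried over from the SCI section, and equal taught hours in the two arms. The gap in coached contact does not depend on either.

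The randomised contrast estimates the whole CCC package versus generic information. It cannot attribute a difference to curriculum content or behavioural support with attention held constant. The limit matters most for the self-reported half of the caregiver measures and for Objective III.

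It would be a mistake to extend the point to the primary outcome. Body mass in SCI participants is assessed as a pre-post change, and all of them receive the lifestyle intervention, so the caregiver control label does not enter that analysis.

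**What to change.** 1. In Section 4.4, limit the attention/time-controlled label to the taught sessions, and say that supervised exercise, diet prescription and coach contact are not matched.
2. Describe the CCC in the same terms in the Abstract, Section 4.4 and Section 6.2, as an exercise, diet and behavioural package. Make clear in the Abstract which caregivers receive it.
3. In Section 6.2, define the similar schedule by planned contact hours per arm, split into taught, supervised and unsupervised time, and state the number of weeks in the CCC programme consistently.
4. Word Objectives II and III, and Hypothesis III, as effects of the whole package compared with generic information.
5. Report actual contact time by arm and component beside the caregiver self-report outcomes.

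The cost is protocol wording and a simple contact log. The article does not describe session records, so the log may have to be set up. No arm, visit, outcome or sample size changes. The downside is a less favourable description of the control and a narrower claim.

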
### 4.5. Trial Participants/Sample Size

The target sample size to be recruited is based on change in the primary outcome measure of body mass in the SCI group. Effect size was calculated based on statistical guidelines established by Cohen [38], similar SCI-related body mass reduction interventions [39], and ES in terms of relative risk reduction for the DPP [29]. Given a significant moderate ES of 0.48, for a two-tailed Fisher’s least significant difference test based on the difference between pre- and post-TLI body mass, with an α = 0.05 and power of 1-β ≥ 0.90, we calculated sample size (N) would require N ≥ 24 per group.

We targeted the enrollment of 30 dyadic couples (30 SCI; 30 caregivers = 60) who satisfy the inclusion and exclusion criteria (outlined below). We assumed an attrition of 20%, yielding an analytic sample size of 48. We note that preliminary data specific to this type of multi-modal and comprehensive TLI in SCI are not available for a direct calculation of ES. It is important to note that power analyses are estimates and assumptions about the effect sizes, and other parameters can vary. Additionally, other factors such as variability in participant characteristics, study design, and protocols can influence statistical power. In this study, we maintain alignment with standard statistical practice and fidelity to the DPP primary trial outcome, body mass, measured before and after the clinical intervention and extension phase.

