Therapeutic lifestyle intervention (TLI)—involving a combination of physical activity, healthy nutrition, stress management techniques, and educational interventions—typically results in improved overall health and well-being. To address these needs, the Diabetes Prevention Program (DPP) was a landmark NIH-sponsored, 27-center randomized clinical trial that tested a lock-step lifestyle intervention program for persons who were at risk of developing T2DM. The DPP was found to be effective for promoting body mass reduction and lessening the conversion rates to frank diabetes [27,28] and was favorably compared against first-line pharmacotherapy for T2DM [29]. Importantly, programmatic modification of the DPP and testing of the long-term follow-up have shown remarkable success in sustaining—or even further improving—the benefits obtained during the initial treatment. The existing evidence similarly suggests an important role for ‘weight-lowering and fitness-promoting nutrition and exercise’ lifestyle interventions to improve the health and function of people aging with disability [30,31]. Previous studies have emphasized the need for weight management in SCI [32,33], and notably, a preliminary case series in which the DPP was refashioned for persons with SCI found that a clinically significant loss of body mass effectively reduced the component risks for CMD and diabetes [26]. In this way, TLI may be a promising approach for CMD management in SCI that merits further research to fully understand its potential benefits, sustainability, and optimal implementation strategies.

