2.6-Month Nutritional Intervention: The nutritional intervention for the trial will consist of a 24-week energy-restricted Mediterranean-style diet. In accordance with the DPP study [74] and ADA guidelines [75], we will ensure that the participants have the daily energy consumption necessary to maintain baseline body weight and consider physical activity energy expenditure. The daily energy intake will be reduced to achieve a 500–1000 kcal/d deficit. This is sufficient to result in a weight loss of 1–2 lbs/week and approximately 7% of baseline body mass by the end of the 24-week intervention. The approximate target daily energy intakes prior to the adjustment for physical activity will be 1200 kcal/d for subjects weighing 120–170 lbs at baseline, 1500 kcal/d for subjects weighing 175–215 lbs at baseline, 1800 kcal/d for subjects weighing 220–245 lbs at baseline, and 2000 kcal/d for subjects weighing more than 250 lbs at baseline. The experimental nutrition will emphasize fruits, vegetables, whole grains, and olive oil, while animal sources of protein will be restricted to poultry and fish. The daily energy intake will be composed of 45–50% carbohydrate, 15% protein, and 35–40% fat. The daily fat intake will consist primarily of monounsaturated fats (18–20% of the daily energy intake) from olive oil (30–50 g/d, ~2.2–3.7 tbsp) and tree nuts (<20 g/d), with only a small portion from saturated fats (<7%) and the balance from polyunsaturated fats (10–13%). This macronutrient composition closely resembles those used by several recent investigations of Mediterranean-style nutrition [76,77,78]. While the relative carbohydrate consumption appears low (45–50% of daily energy intake), a lower-carbohydrate Mediterranean-style diet (<50%) results in greater body weight losses among obese women than higher-carbohydrate Mediterranean-style diets (>50%). In accordance with ADA guidelines, the intake of trans-fat will be minimized, the daily cholesterol intake will be limited to <200 mg/d, and the fiber intake will be targeted at 14 g/1000 kcal consumed.

A nutritional education and assessment will teach subjects food intake self-monitoring skills by using scales, measuring cups, and spoons provided to them for home use. Nutrition booklets will be provided, which will include information on common food items, food groups, servings, sample day-to-day menus, recipes, and food logs.

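### The 0.48 effect size in section 4.5 rests partly on a relative risk reduction and has no stated standardiser; as a paired effect it gives about 62% power with 24 SCI completers, not 90%

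*Protocol article*

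**What the plan says.** Section 4.5 says the target sample size "is based on change in the primary outcome measure of body mass in the SCI group". Three sources are named for the effect size: general guidelines on effect sizes, similar body-mass interventions in SCI, and "and ES in terms of relative risk reduction for the DPP [29"].

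The planned test is described as a "two-tailed Fisher’s least significant difference test based on the difference between pre- and post-TLI body mass". The effect size entered is 0.48, which the section calls moderate; the significance level is 5% and the power sought is 90% or more. The result is at least 24 per group. Enrolment is 30 SCI participants and 30 caregivers, and 20% attrition leaves 48 for analysis.

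The section concedes that "preliminary data specific to this type of multi-modal and comprehensive TLI in SCI are not available for a direct calculation of ES". It gives no mean change, SD or pre/post correlation behind 0.48.

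Under section 4.4 only caregivers are randomised and every SCI participant receives the lifestyle programme. The SCI pre/post test therefore has a single group.

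**The concern.** There are two linked problems.

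- **The kind of quantity.** The standardised effect for a pre/post test on a continuous outcome is a mean change divided by an SD. A relative risk reduction compares event probabilities. It has no SD in kilograms or percent and does not turn into a body-mass effect without a model, which the section does not offer.
- **The missing standardiser.** An effect size of 0.48 means one thing on the SD of change and another on the between-person SD at baseline. The power differs greatly between the two, and section 4.5 does not say which is meant.

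At stake is the claim of at least 90% power for the primary outcome. As written, a reader cannot tell what body-mass loss the trial can detect, and on the natural reading the claim is not met.

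**Working it through.** **Inputs, all from section 4.5:** effect size 0.48; two-sided α = 0.05; power 0.90; 24 per group; 30 + 30 enrolled; 20% attrition. Completers: 60 × 0.8 = 48 people, that is 30 × 0.8 = 24 SCI and 24 caregivers.

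**Step 1. Try to reproduce 24 with the described test.** With two time points, Fisher's LSD is the paired t-test. Taking d = mean change / SD of change:

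- Normal approximation: n = (1.960 + 1.282)² / 0.48² = 10.51 / 0.2304 = 45.6, so 46 pairs.
- Exact (noncentral t): 48 pairs, with power 90.3%.

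The stated 24 is not reproduced. Other readings of the test:

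| Reading of 0.48 | n for 90% power |
|---|---|
| Paired, two-sided | 48 pairs |
| Paired, one-sided | 39 pairs |
| Paired, two-sided, 80% power instead | 37 pairs |
| Two-sample, two-sided | 93 per group |
| Cohen's f = 0.48 (d = 0.96), two-sample | 24 per group (power 90.2%) |

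The last row matches 24 per group, but it is a comparison of two independent groups and not the pre/post test described. The paired answer of 48 equals the analytic total, but that total contains only 24 SCI participants.

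**Step 2. Power of the described test at 0.48.** Paired t, two-sided 0.05:

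| SCI pairs | Power |
|---|---|
| 24 | 61.5% |
| 30 (no attrition) | 71.9% |
| 48 | 90.3% |

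Pooling the error term over more visits would add degrees of freedom but changes little. Even with the SD treated as known, power at 24 is Φ(0.48 × √24 − 1.960) = Φ(2.352 − 1.960) = Φ(0.392), about 65%.

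With 24 pairs, 90% power needs a standardised change of 0.69; with 30 pairs it needs 0.61. To finish with 48 SCI completers at 20% attrition, 48 / 0.8 = 60 SCI participants would have to be enrolled.

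**Step 3. If 0.48 is on the baseline SD.** With equal SDs before and after and correlation r, the paired effect is 0.48 / √(2(1 − r)). The values of r are assumptions, since none is given.

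| r | Paired effect | Power, 24 pairs |
|---|---|---|
| 0.5 | 0.48 | 61.5% |
| 0.6 | 0.54 | 71.2% |
| 0.7 | 0.62 | 82.8% |
| 0.75 | 0.68 | 88.9% |
| 0.8 | 0.76 | 94.5% |
| 0.9 | 1.07 | 99.9% |

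The break-even for 90% is r = 1 − (0.48 / 0.691)² / 2 = 0.76.

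**Step 4. What a range over the SD would look like.** Section 6.1 expects a loss of "approximately 7% of baseline body mass by the end of the 24-week intervention". Using 7% only as an illustration, with 24 pairs and assumed SDs of change:

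| SD of change (% of baseline) | Paired effect | Power |
|---|---|---|
| 8 | 0.88 | 98.4% |
| 10 | 0.70 | 90.7% |
| 12 | 0.58 | 78.1% |
| 14.6 (= 7 / 0.48) | 0.48 | 61.5% |

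**The case against.** The strongest reply is that 0.48 may be on the baseline SD. Repeated weights in the same person are usually highly correlated, so a correlation above 0.76 is plausible and 24 pairs would then suffice. That stands as a possibility, and it is why the trial cannot be called underpowered outright. It does not rescue the text, because neither that standardiser nor a correlation is stated and the power claim turns on them.

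A second reply is that a journal article condenses the derivation, that relative risk reduction is one of three sources, and that the section admits its effect size is an assumption. The derivation may indeed sit elsewhere. But the article itself names a source of the wrong kind, and it prints an effect size, power and n that do not agree under the test it describes.

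Two stronger readings are tempting, and the documents do not support them.

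- **A conflict between 0.48 and the 7% loss.** The 7% is a diet target in section 6.1, not a sizing input, and no SD is documented, so no conflict is shown. A planning effect smaller than the treatment target is ordinary caution. If a 7% loss is achieved with an SD of change up to about 10%, 24 pairs keep at least 90% power.
- **A denial that preliminary data exist.** The Introduction reports "a preliminary case series in which the DPP was refashioned for persons with SCI found that a clinically significant loss of body mass" reduced cardiometabolic risks. Section 4.5 says only that data do not allow a direct calculation of the effect size. A case series can report benefit without giving a usable SD of change, so the two statements are compatible.

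**Conclusion.** The point holds in two parts. First, relative risk reduction is not a valid source for a standardised body-mass change, and no conversion is given. Second, the stated power of at least 90% is not delivered on the natural reading of 0.48. It is about 62% with 24 SCI completers, 28 to 29 points short, and 48 SCI completers are needed, twice the number planned.

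This rests on reading 0.48 as mean change over SD of change in a two-sided paired test at 0.05 in SCI participants alone. On the baseline-SD reading the claim is met only if the pre/post correlation is about 0.76 or more. What is established is that the stated power is unsupported as written. Whether the trial will in fact miss a worthwhile loss cannot be told without an SD. This should be corrected, but it does not invalidate the design.

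**What to change.** In section 4.5:

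1. Delete relative risk reduction as a source of the effect size.
2. State the planned mean body-mass change and the SD of within-person change, or the baseline SD and pre/post correlation, with the source of each. The SCI body-mass interventions already cited are the natural place to look.
3. Say what 0.48 is standardised by, or replace it.
4. Restate the power for 24 SCI completers, without counting caregivers. If 0.48 is kept as a paired effect, this is about 62%, with 0.69 needed for 90%. Otherwise give a short range over assumed SDs, as in step 4 of the working.

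The cost is one paragraph and a short recalculation, with no change to procedures. The downside is a stated power that is less favourable or given as a range. Enrolment need not change to make this correction. If the sponsor wants to keep 90% at a paired effect of 0.48, that would take 60 SCI participants at 20% attrition instead of 30, which is a separate decision.
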